| Duration of Participation: | 40 weeks; including a screening period up to 4 weeks, a 5-week re-boosting period (re-boosting and DTH at Visit 2, re-boosting at Visit 3 and DTH at Visit 4) followed by 8 weeks before cessation of ART (Visit 5), and then a 16 week ART-free follow-up period. At Visit 9, ART will be re-started and the subjects will be followed for an additional 8 weeks.                                                                                                                                                                                                                                                                                                                                                                                                                                                                                                                                                                                                                                                                                                                                                                                                                                                                                                                                                                                                                                                                                                                                                                                                                                                                                                                                                                                                                                                                                                                                                                                                                                                                                                                                                                                                                                                                                                                                                                                                                                                                                                                     |
| Endpoints:                 | 
Primary efficacy endpoints:
 
 
• Viral load set point (mean of VL count Visit 8 and 9) for subjects discontinuing ART according to protocol and not resuming ART until visit 9 compared to: 
 
- viral load set point* for subjects not resuming ART before week 52 or later in the CT-BI Vacc-4x 2007/1 study and who entered this study,
 
or if week 52 not reached in the previous study
 
- viral load set point** for subjects resuming ART at the earliest week 40 in the CT-BI Vacc-4x 2007/1 study and who entered this study.
 
 
 
 
* The VL set point was defined as the mean of VL count between week 48 and week 52 in subjects who did not resume ART.
 
**The VL set point was defined as the week 40 VL count for subject resuming ART week 40 or the mean of the last two VL counts prior to ART resumption for subjects resuming ART week 44 or later but before week 52.
 
Comparison will also be made to pre-ART viral load values, if available from the CT-BI Vacc-4x 2007/1 study.
 
 
• T-cell response will be measured by ELISPOT as well as by T-cell proliferative response assay (Flow Cytometry) and intracellular cytokine staining at Visit 2 (before re-boosting), Visit 4 (28±2 days after re-boosting), Visit 6, Visit 9 and Visit 10. These will be compared to the responses reported in the study CT-BI Vacc-4x 2007/1.
 
 
Secondary efficacy endpoints:
 
 
• CD4 counts at all visits in the study, absolute numbers of CD4 counts, and treatment emergent changes in CD4 counts from mean at Screening and Week 1.
 
• Change (and percent change) in CD4 count from Visit 5 (ART discontinued) to Visit 6, 7, 8, 9 and 10.
 
• CD8 counts at all visits in the study, absolute numbers of CD8 counts, and treatment emergent changes in CD8 counts from mean of Screening and Visit 2.
 
• Change (and percent change) in CD8 count from Visit 5 (ART discontinued) to Visit 6, 7, 8, 9 and 10.
 
 
For each individual subject both the absolute and relative changes in CD4 and CD8 values registered at Visit 5, and at Visit 9 (or the last value before reinitiated ART, if ART reinitiated before Visit 9) will be compared with the corresponding values
 |

|                             |                                                                                                                                                                                                                                                                                                                                                                                                                                                                                                                                                                                                                                                                                                                                                                                                                                                                                                                                                                                                                                                                                                                                                                                                                                                                                                                                                                                                                                                                                                                                                                                                                                                                                                                                                                                                                                                                                                                                                                                                                                                                                                                                                                                                                                                                                                                                                                                                                                                                                                                                                                       |
|-----------------------------|-----------------------------------------------------------------------------------------------------------------------------------------------------------------------------------------------------------------------------------------------------------------------------------------------------------------------------------------------------------------------------------------------------------------------------------------------------------------------------------------------------------------------------------------------------------------------------------------------------------------------------------------------------------------------------------------------------------------------------------------------------------------------------------------------------------------------------------------------------------------------------------------------------------------------------------------------------------------------------------------------------------------------------------------------------------------------------------------------------------------------------------------------------------------------------------------------------------------------------------------------------------------------------------------------------------------------------------------------------------------------------------------------------------------------------------------------------------------------------------------------------------------------------------------------------------------------------------------------------------------------------------------------------------------------------------------------------------------------------------------------------------------------------------------------------------------------------------------------------------------------------------------------------------------------------------------------------------------------------------------------------------------------------------------------------------------------------------------------------------------------------------------------------------------------------------------------------------------------------------------------------------------------------------------------------------------------------------------------------------------------------------------------------------------------------------------------------------------------------------------------------------------------------------------------------------------------|
|                             | 
registered at Week 28 (ART discontinued) and Week 52 (or last visit before ART re-initiation) in the initial study CT-BI Vacc-4x 2007/1 (EudraCT Number 2007-006302-13).
 
 
• DTH (both induration and erythema) at Visit 2 and Visit 4, in terms of observed areas (<math>\text{mm}^2</math> length x height) and also in terms of a positive test, defined as an area <math>\geq 10\text{mm}^2</math> DTH-tests, both areas and number of positive tests registered at Visit 2 will be compared with the corresponding values registered at Visit 4.
 
 
In addition the values for these DTH parameters at Week 5 will be compared with the DTH response reported at Week 18 in the initial study CT-BI Vacc-4x 2007/1 (EudraCT Number 2007-006302-13).
 
Safety endpoints:
 
 
• Proportion of subjects who experience similar virologic suppression 8 weeks after re-initiation of ART (Visit 10) as before ART interruption (Visit 5 value).
 
• AEs, recorded continuously from Screening to Visit 10 (End of Study).
 
• Vital signs (heart rate, blood pressure) at Screening, and selected visits through Visit 10 (End of Study).
 
• Clinical laboratory evaluations (clinical chemistry, hematology) at screening, and selected visits through Visit 10 (End of Study); absolute values and treatment emergent changes from mean at Screening and Visit 2.
 
                                                                                                                                                                                                                                                                                                                                                                                                                                                                                                                                                                                                                                                                                                                                                                                                                                                                                                                                                                                                                                                       |
| Statistical Methods: | 
All subjects who receive at least one re-boosting immunization will be included within the safety population. All safety analyses will be conducted on the safety population. All subjects who receive at least one re-boosting immunization and have any post-baseline efficacy data will be included in the ITT population. Unless otherwise indicated, all efficacy analyses will be conducted on the ITT Population. All ITT subjects who receive two re-boosting immunizations discontinue ART at Week 13 (as planned) and who do not incur a major protocol violation that would challenge the validity of their data will be included within the PP population. All efficacy analyses will also be conducted on the PP population. No interim analysis is planned.
 
In general continuous variables will be described using number of observations (n), mean, standard deviation (SD), geometric mean, minimum, maximum, median, and quartiles. Categorical data will be presented using counts (n) and percentages (%). All statistical analyses will be performed using appropriate procedures in SAS Software Version 9.2 or higher. Significance of effects will be determined by two-sided tests with p-value < 0.05.
 
All analyses will be carried out after all participants have completed Visit 10 (or early withdrawal from study) and the study database has been authorized by the Sponsor as complete and final, and protocol deviations have been identified.
 
The primary efficacy endpoint of this study is the comparison of the re-boost viral load set-point after re-boosting and a 16 week ART-free period with the viral load set-point reported in the initial CT-BI Vacc-4x 2007/1 study (EudraCT Number 2007-006302-13). The primary comparison will be a Wilcoxon signed rank test comparing changes in viral load between the two stated comparison values. The re-boost viral load set-point will also be compared to the pre-ART viral load value, if available from the study CT-BI Vacc-4x 2007/1. The co-primary endpoint of this study is the T-cell response to Vacc-4x and/or p24 which will be measured by ELISPOT as well as by T-cell proliferative response assay (flow cytometry) and intracellular cytokine staining at Visit 2 (before re-boosting), Visit 5 (two weeks after re-boosting), Visit 6, 9 and 10 (End of Study). These responses will be compared to the T-cell response reported in the initial study CT-BI Vacc-4x 2007/1 (EudraCT Number 2007-006302-13) using McNemar's
 |

|  |                                                                                                                                                                                                                                                                                                                                                                                                                                                                                                                                                                                                                                                                                                                                                                                                                                                                                                                                                                                                                                                                                                 |
|--|-------------------------------------------------------------------------------------------------------------------------------------------------------------------------------------------------------------------------------------------------------------------------------------------------------------------------------------------------------------------------------------------------------------------------------------------------------------------------------------------------------------------------------------------------------------------------------------------------------------------------------------------------------------------------------------------------------------------------------------------------------------------------------------------------------------------------------------------------------------------------------------------------------------------------------------------------------------------------------------------------------------------------------------------------------------------------------------------------|
|  | 
test. Secondary efficacy endpoints for CD4, CD8, and DTH (induration and erythema) parameters will be defined based on scheduled visit assessments post start of study medication, to be compared to results from the initial study CT-BI Vacc-4x 2007/1 (EudraCT Number 2007-006302-13). Continuous data types will be analyzed using the Wilcoxon signed rank test, binary data types using McNemar's test. Safety will be assessed through the collection of AE reports, assessing virologic suppression, vital signs, and laboratory evaluations that are commonly employed in clinical studies. Visit 2 safety data will be used for comparison with the data obtained during the study period. Summary statistics will be prepared for measured values and change from Visit 2 values. Virologic suppression will be assessed between the timing of ART interruption and ART re-initiation. Summaries of treatment-emergent clinically important abnormalities in vital signs and laboratory data will be provided. No statistical testing will be performed on safety parameters.
 |
|--|-------------------------------------------------------------------------------------------------------------------------------------------------------------------------------------------------------------------------------------------------------------------------------------------------------------------------------------------------------------------------------------------------------------------------------------------------------------------------------------------------------------------------------------------------------------------------------------------------------------------------------------------------------------------------------------------------------------------------------------------------------------------------------------------------------------------------------------------------------------------------------------------------------------------------------------------------------------------------------------------------------------------------------------------------------------------------------------------------|

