| Treatment Regimen:         | Subjects will receive re-boost immunizations of 1.2 mg Vacc-4x + 0.06 mg Leukine® (sargramostim, recombinant human Granulocyte Macrophage Colony Stimulating Factor [rhu-GM-CSF], adjuvant) at Visit 2 and 3 (15±2 days between the immunizations). At Visit 5, eligible subjects whose CD4 count is $\geq 350 \times 10^6/L$ and virally controlled are expected to discontinue ART and will be followed for an additional 16 weeks without ART (at Visit 9 recommencement of ART will be recommended).                                                                                                                                                                                                                                                                                                                                                                                                                                                                                                                                                                                                                                                                                                                                                                                                                                                                                                                                                                                                                                                                                                                                                                                                                                                                                                                                                                                                                                                                                                                                                                                                                                                                                                                                                                                                                                                                                                                                                                               |

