## **1.6 Potential Risks and Benefits**

Participants will provide important scientific information that may contribute to improved future vaccination of HIV-positive subjects. Potential benefits for participants include a possible sustained improvement in the immune response to p24 and HIV. Potential risks include the discomfort and inconvenience associated with the immunizations and the risk of known or unknown side effects of exposure to Vacc-4x and Leukine® including, most commonly, local reactions at the site of injections and fatigue (incidence not yet determined). However, since all subjects in this study have participated in Study CT-BI Vacc-4x 2007/1 (EudraCT Number 2007-006302-13) they are aware of potential discomfort.

Interruption of ART for extended periods is associated with an increased morbidity and mortality, thus planned long-term therapy interruption strategies are not recommended outside of controlled clinical trials (Department of Health and Human Services [DHHS] Guidelines for the Use of Antiretroviral Agents in HIV-infected Adults and Adolescents, January 29, 2008). In the present study the subjects are stopping ART for a relatively short period of up to 16 weeks, during which they will be closely monitored.

The subjects will remain on ART throughout the immunization period and for another 10 weeks after the final immunization, in order to prevent interference from the immune response caused by viral rebound associated with ART interruption. In all studies with Vacc-4x, subjects have been vaccinated when on ART with no loss of viral control. Viral rebound was only observed after subjects stopped ART. During the ART interruption period, subjects are being monitored carefully and ART will be restarted if subjects exceed pre-specified criteria for viral load and CD4 reduction or for any other medical reasons (4.4.1.3 Criteria for Restart of ART).

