## **3 STUDY DESIGN**

### **3.1 Overall Study Design and Flow Chart**

The study is an open label, multicenter, follow-up, re-boosting study of subjects who previously completed the immunization regimen with Vacc-4x active and stopped ART (at Week 28) in the CT-BI Vacc-4x 2007/1 Study (EudraCT Number 2007-006302-13). No restart of ART is required. The subjects will be re-boosted with two immunizations (Visit 2 and Visit 3) of Vacc-4x, 1.2 mg peptides (12 mg/mL), with a 2 week interval between immunizations.

At Visit 5 ART medication (if being used) will be stopped in subjects whose CD4 count  $\geq 350 \times 10^6/\text{L}$ , for a 16 week period. At Week 29 ART will be restarted, according to the Investigator and subject's decision, and the subjects will be followed for an additional 8 weeks (End of Study; Visit 10).

DTH will be measured at Visit 2, and at Visit 4 (3 weeks after the second re-boosting immunization).

Viral load, CD4 and CD8 counts will be measured at all study visits. T-cell responses will be measured at Visits 2, 4, 6, 9 and 10 (End of Study) both by ELISPOT, T-cell proliferation assay and intracellular cytokine staining.

Vital signs and clinical laboratory tests will be done at all study visits.

Monitoring of AEs and concomitant medications will be done continuously from the time of signing ICF through the End of Study.

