**Table 1. Time and Events Schedule**

| Parameters                                                | Screening/
Verification
Inclusion | Re-vaccination cycle |                |      |                     |                           |       |       |                       | Follow-up       |
|-----------------------------------------------------------|-----------------------------------------|----------------------|----------------|------|---------------------|---------------------------|-------|-------|-----------------------|-----------------|
|                                                           |                                         | Re-boost period      |                |      | Follow-up
on ART | ART-free follow-up period |       |       |                       | END of
STUDY |
| Visit:                                                    | 1                                       | 2                    | 3              | 4    | 5                   | 6                         | 7     | 8     | 9                     | 10              |
| Day                                                       |                                         | 1                    | 15±2           | 28±2 | 84±3                | 112±7                     | 140±7 | 168±7 | 196±7                 | 252±7           |
| Week                                                      | -4                                      | 0                    | 2              | 4    | 12                  | 16                        | 20    | 24    | 28                    | 36              |
| Re-boost: Adjuvant + Vacc-4x                              |                                         | x                    | x              |      |                     |                           |       |       |                       |                 |
| DTH a                                          |                                         | x                    |                | x    |                     |                           |       |       |                       |                 |
| ART status                                                | On or Off                               |                      |                |      | Stop g   |                           |       |       | Re-start h |                 |

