| Adverse Events                                            | x                                       | x                    | x              | x    | x                   | x                         | x     | x     | x                     | x               |
| Concomitant Medications                                   | x                                       | x                    | x              | x    | x                   | x                         | x     | x     | x                     | x               |

a. Immunization for the DTH skin reaction is performed on day indicated; the test is evaluated 48 hours after immunization. This evaluation can be made by the subject, if properly trained.

b. Height only once at Screening.

c. Includes measurements of hemoglobin, CRP, WBC, platelets, creatinine, AST (SGOT), ALT (SGPT), LDH, ALP, γ-GT, albumin, total bilirubin, and β2-microglobulin.

d. Viral load will be quantified by HIV RNA copies/mL using PCR. CD4 and CD8 counts will be determined using flow cytometry.

e. T-cell response will be measured by ELISPOT as well as T-cell proliferative response assay and intracellular cytokine staining.

f. A urine pregnancy test will be administered and a negative test will be confirmed, prior to study drug administration.

g. If on ART subjects whose CD4 count is  $\geq 350 \times 10^6/L$  and virally controlled at Visit 5 are expected to stop ART.

h. Restart according to Investigator's/subject's decision.

i. Blood samples should be taken before immunization (re-boosting).

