#### **6.3.3.4 Visit 9**

This visit should be 196 ( $\pm 7$ ) days from Visit 2.

At this visit it will be recommended that the subjects restart ART.

The following procedures will be performed:

- Review of concomitant medications and AEs.
- Physical examination including weight.
- Vital signs (blood pressure, heart rate).
- Clinical chemistry and hematology.
- Viral load, proviral DNA, CD4 and CD8 counts.
- T-cell response (ELISPOT, T-cell proliferative response assay and intracellular cytokine staining).

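### ART restart at Visit 9 is unconditional in one synopsis row but recommended or discretionary elsewhere, while the last study phase, a safety endpoint and the 16-week risk statement assume that every subject restarts

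*Protocol*

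**What the plan says.** The protocol states the status of ART after Visit 9 in five places.

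- Synopsis, Duration of Participation: "At Visit 9, ART will be re-started and the subjects will be followed for an additional 8 weeks".
- Synopsis, Treatment Regimen: "at Visit 9 recommencement of ART will be recommended".
- Section 3.1: "At Week 29 ART will be restarted, according to the Investigator and subject's decision, and the subjects will be followed for an additional 8 weeks".
- Table 1, footnote h: "Restart according to Investigator's/subject's decision".
- Section 6.3.3.4 (Visit 9): "At this visit it will be recommended that the subjects restart ART".

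Four other parts depend on that status.

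- Sections 6.1 and 6.3.4 define the last phase as the eight weeks that follow restart.
- Sections 2.2.2 and 10.6.3.2 define a safety endpoint that compares viral suppression at Visit 10, described as eight weeks after ART is resumed, with suppression at Visit 5.
- Section 1.6 describes subjects as "stopping ART for a relatively short period of up to 16 weeks, during which they will be closely monitored".
- Section 4.4.1.3 lists the criteria for resuming ART while it is interrupted. Three of the five rest on CD4 count or viral load.

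Section 10.5 provides for describing subjects who stop or restart ART at other scheduled visits. It adds no visit and no test.

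**The concern.** Under the unconditional wording, a subject still off ART after Visit 9 has departed from the protocol. Under the other wordings the same subject complies. The protocol permits the second case but describes its last phase, one safety endpoint and its risk statement only for the first.

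Three things are at stake:

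- whether the stated limit and monitoring of the interruption are accurate for everyone the protocol allows to stay off ART;
- whether the numerical restart criteria can work in the last eight weeks;
- whether the suppression endpoint has a meaning for a subject who has not restarted, or who restarted at another time.

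The case is not far-fetched. Subjects may enter the study already off ART (Section 4.2, Table 1), and Section 1.4 reports that most subjects of the earlier Phase II study stayed off ART after that study ended.

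**Working it through.** **Inputs**

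- Table 1 and Section 6.3, days from Visit 2: Visit 5 at 84±3, Visit 6 at 112±7, then "140±7 | 168±7 | 196±7" for Visits 7 to 9, and Visit 10 at 252±7.
- Section 6.3.2.4: ART is stopped once the Visit 5 results are seen, with the instruction given within one week. I take the stop as 0 to 7 days after Visit 5.

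**The plan's own figures**

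- Visit 5 to Visit 9: (196 − 84)/7 = 16 weeks.
- Visit 9 to Visit 10: (252 − 196)/7 = 8 weeks.
- Visit 9: 196/7 = Week 28, as in Table 1.

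The 16-week interruption and the 8-week follow-up are reproduced for a subject who restarts at Visit 9.

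**Time off ART for a subject who does not restart (nominal days)**

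- Stop on the day of Visit 5: (252 − 84)/7 = 24 weeks at Visit 10.
- Stop 7 days later: (252 − 91)/7 = 23 weeks.

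That is 7 to 8 weeks beyond the 16 stated in Section 1.6.

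**Interval between scheduled CD4 and viral-load tests**

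- Visits 5 to 9: 28 days each (112 − 84, 140 − 112, 168 − 140, 196 − 168).
- Visit 9 to Visit 10: 252 − 196 = 56 days. With windows, the shortest gap is (252 − 7) − (196 + 7) = 42 days and the longest is (252 + 7) − (196 − 7) = 70 days.

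The nominal gap doubles at the point where the interruption passes its stated maximum.

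**Reach of the restart criteria (4.4.1.3) between Visits 9 and 10**

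- The three numerical criteria are CD4 below the threshold, a CD4 fall of at least half, and viral load above the limit on two tests. A value that first crosses after Visit 9 meets no scheduled test before Visit 10. A value already over the line at Visit 9 would call for a retest within two weeks, which falls inside the gap.
- The other two criteria are HIV- or AIDS-related events and investigator judgement. They need no scheduled test.

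**Safety endpoint**

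- Restart at Visit 9: Visit 10 falls 56/7 = 8 weeks after restart, so the definition holds.
- Restart earlier, for example at Visit 7: (252 − 140)/7 = 16 weeks, so Visit 10 is not the stated time point.
- No restart: the time point does not exist.

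**Week labels**

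- Section 3.1 says Week 29 and Table 1 gives Week 28. The synopsis statistical text puts ART discontinuation at Week 13, where Table 1 has Week 12, and 13 + 16 = 29. This looks like an older numbering.
- The synopsis periods add to 4 + 5 + 8 + 16 + 8 = 41 weeks against the stated 40. Table 1 gives 4 + 36 = 40.

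**The case against.** The strongest reply is that little of this is a true contradiction. A recommendation and a decision by investigator and subject are compatible: the protocol advises and they decide. Section 3.1 puts the firm wording and the decision in one sentence, so only the Duration of Participation row is unqualified. That is right, and it narrows the conflict to one firm statement against a consistent optional reading. It does not explain why Sections 6.1, 6.3.4, 2.2.2 and 10.6.3.2 are written as if restart were universal.

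A reader might infer that subjects who stay off ART go eight weeks unmonitored. The documents do not support that. Adverse events and concomitant medication are recorded continuously to the end of study (3.1). Visits 9 and 10 both include examination, laboratory tests, CD4 and viral load. Two restart criteria need no scheduled test, and care outside the protocol is not excluded.

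A reader might also infer that the visit plan can work only if ART is restarted. That too goes beyond the text. Visit 10 is counted from Visit 2 and can be held for anyone. An equal 56-day gap (Day 28 to Day 84) already applies to subjects who enter off ART.

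Section 1.6 can be read as describing only the interruption that the study asks for, Visit 5 to Visit 9. On that reading it needs a qualifier rather than a retraction, but as written it makes no such limit.

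Finally, a statistical analysis plan, not available here, may say how non-restarters enter the suppression analysis. It could not settle restart status, the risk statement or the visit schedule.

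**Conclusion.** The point holds in this form. Restart at Visit 9 is unconditional in one synopsis row and recommended or discretionary elsewhere, while the phase definitions and the virologic-suppression endpoint assume that it always happens. For a subject permitted to stay off ART:

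- time off ART reaches about 23 to 24 weeks by Visit 10, against a stated maximum of 16;
- no visit, CD4 count or viral load is scheduled for 56 days (42 to 70), so a new numerical crossing after Visit 9 would not be found by a scheduled test;
- the suppression endpoint has no defined time point.

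The 23 to 24 weeks rest on nominal visit days and on ART being stopped 0 to 7 days after Visit 5. The documents do not say how many subjects would decline restart, so the number affected is unknown. The Week 28/29 and 40/41-week differences are minor, because Day 196 fixes Visit 9 in any case. The matter is more than clerical, since it touches the stated risk and a safety endpoint, and it should be corrected.

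**What to change.** Reconcile both synopsis rows (Treatment Regimen, Duration of Participation), Sections 1.6, 3.1, 6.1, 6.3.3.4 and 6.3.4, and Table 1 footnote h to one statement of restart status and one week label for Visit 9.

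If restart remains optional:

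- correct the 16-week and monitoring statement in Section 1.6 so that it is true for subjects who stay off ART;
- reconcile the Visit 9 to Visit 10 schedule with the restart criteria in 4.4.1.3;
- define the endpoint in 2.2.2 and 10.6.3.2 for subjects who have not restarted by Visit 10 and for those who restarted at a time other than Visit 9.

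Which restart rule applies, and what the schedule then requires, is a clinical choice for the sponsor; none is proposed here. The reconciliation itself costs only protocol wording. Any further cost depends on the rule the sponsor chooses.
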